## Abstract

**Introduction:**

To date, there is no consensus on which anterior surgical technique is more cost-effective in treating cervical degenerative disc disease (CDDD). The most commonly used surgical treatment for patients with single- or multi-level symptomatic CDDD is anterior cervical discectomy with fusion (ACDF). However, new complaints of radiculopathy and/or myelopathy commonly develop at adjacent levels, also known as clinical adjacent segment pathology (CASP). The extent to which kinematics, surgery-induced fusion, natural history, and progression of disease play a role in the development of CASP remains unclear. Anterior cervical discectomy with arthroplasty (ACDA) is another treatment option that is thought to reduce the incidence of CASP by preserving motion in the operated segment. While ACDA is often discouraged, as the implant costs are higher while the clinical outcomes are similar to ACDF, preventing CASP might be a reason for ACDA to be a more cost-effective technique in the long term.

**Methods and analysis:**

In this randomized controlled trial, patients will be randomized to receive ACDF or ACDA in a 1:1 ratio. Adult patients with single- or multi-level CDDD and symptoms of radiculopathy and/or myelopathy will be included. The primary outcome is cost-effectiveness and cost-utility of both techniques from a healthcare and societal perspective. Secondary objectives are the differences in clinical and radiological outcomes between the two techniques, as well as the qualitative process surrounding anterior decompression surgery. All outcomes will be measured at baseline and every 6 months until 4 years post-surgery.

**Discussion:**

High-quality evidence regarding the cost-effectiveness of both ACDA and ACDF is lacking; to date, there are no prospective trials from a societal perspective. Considering the aging of the population and the rising healthcare costs, there is an urgent need for a solid clinical cost-effectiveness trial addressing this question.

**Trial registration:**

ClinicalTrials.gov NCT04623593. Registered on 29 September 2020.

**Supplementary Information:**

The online version contains supplementary material available at 10.1186/s13063-022-06574-5.

## Article summary

### Strengths and limitations of this study

External validity and generalizability are limited, as costs are country-specific.A broad economic analysis from a societal perspective in the setting of a prospective randomized controlled trial will investigate the cost-effectiveness of ACDA and ACDF for CDDD, resulting in level I evidence.The sample size is based on estimated costs and average yearly incidence of CASP, which may differ from reality.The burden for patients in this study is low, and potential risks in the intervention group (ACDA) are similar to those in the control group (ACDF with stand-alone cages), which is standard care in our center.Since the gap in incidence of additional CASP-related surgery between ACDF and ACDA expands considerably with time, we expect that a difference in costs, if found within the 4-year follow-up period, will also increase over time.

## Introduction

Cervical degenerative disc disease (CDDD) is the degeneration of a cervical intervertebral disc and/or the adjoining vertebral bodies, resulting in clinical symptoms of cervical radiculopathy, myelopathy, myeloradiculopathy, and axial pain. The incidence of degenerative pathologies is significantly increasing as the proportion of elderly in the population is rising [1, 2]. Currently, generalized spinal disc degeneration occurs in more than 90% of adults over 50 years old [3]. This age group now represents 32.8% of the population in Europe and is projected to reach 40.6% by 2050 [2]. In the next 20 years, a significant increase in anterior cervical decompression surgeries is predicted in people aged 45–54, mainly affecting the working population [4–6]. Symptoms of radiculopathy and/or myelopathy lead to restrictions in daily life and loss of professional capability, resulting in absenteeism. Societal healthcare costs are therefore significantly affected by CDDD. Further costs of healthcare are accrued when patients require surgical treatment, combined with associated hospitalization and rehabilitation. Currently, there are several (surgical) treatments for CDDD available. To date, there is no consensus on which surgical technique is more cost-effective in treating CDDD with radiculopathy and/or myelopathy.

One of the most common procedures for treating patients with single- or multi-level CDDD is anterior cervical discectomy with fusion (ACDF) [7, 8], which results in fusion in 95–100% of the cases [9]. Axial pain alone is not considered an indication for surgical treatment in our country. The primary goal of ACD(F) is the relief of symptoms of radiculopathy and/or myelopathy through decompression of neural structures. Fusion in itself is not a requisite to reach this goal. In our center, ACDF with stand-alone cages is the standard procedure for CDDD. Plate constructs are only used in case there are signs of instability (e.g., spondylolisthesis) and additional stabilization is deemed necessary. A common concern regarding ACDF with stand-alone cages is the occurrence of cage subsidence. However, in our recent retrospective cohort of 673 patients, only 1 patient required additional surgery due to subsidence (0.15%) [10]. Good short-term clinical results are achieved for both radiculopathy and myelopathy [9, 11]. Clinical results are independent from the technique used and from the occurrence of fusion [9, 11–13]. However, patient-reported satisfaction gradually decreases in the years following surgery [14, 15]. This is thought to be the consequence of the development of new complaints due to degenerative changes at a segment adjacent to the site of the index surgery, also known as adjacent segment pathology (ASP) [16].

A recent consensus proposes a distinct definition that distinguishes between *radiologic* adjacent segment pathology (RASP) and *clinical* adjacent segment pathology (CASP) [16]. CASP occurs at an estimated cumulative rate of 1.6–4.2% per year after ACDF [16, 17]; however, the incidence reported in literature varies widely [18–21]. Nevertheless, 50–75% of the patients that develop CASP require additional adjacent segment surgery [17, 22–27]. In our retrospective cohort, we observed an average rate of 2.1% of CASP per year, with an additional adjacent segment surgery rate at an average of 1.5% per year [10]. The annual incidence was unevenly distributed as half of these additional surgeries for CASP occurred within 2.5 years, which suggests a peak incidence in the first years following the index surgery [10].

The underlying mechanism of ASP remains a matter of debate. Besides natural progression of degeneration, compensation for the loss of motion in the fused segment is thought to cause overstraining of the adjacent segments [28–30]. Altered cervical sagittal alignment is also thought to be important in the accelerated development of CASP. Indeed, higher rates of CASP are observed after ACD, concomitant with an increased segmental kyphosis at the index level [12, 31, 32]. Unlike ACD, ACDF with plate constructs restores cervical sagittal lordosis. However, a higher rate of ASP is observed in patients with plate constructs compared to ACDF with stand-alone cages [12, 33]. This finding might be explained by the plate causing strain on the adjacent segments, or the more extensive surgical preparation for installing the plate, which increases the chance of iatrogenic damage to the adjacent level. Another contributing factor might be the occurrence of subsidence of the plate construct into the adjacent segment. Disc height at the adjacent segments has been found to be significantly decreased in patients with plate constructs, which supports this theory [33]. Nevertheless, the extent to which altered cervical motion influences the development of ASP remains unknown [34, 35].

Anterior cervical discectomy with arthroplasty (ACDA) was developed as another treatment option for cervical radiculopathy and/or myelopathy to reduce the incidence of CASP by preserving motion in the operated segment. Previously conducted research in patients with radiculopathy and/or myelopathy has shown that clinical and radiological outcomes are similar between ACDA and ACD(F) [28, 36, 37]. A meta-analysis found better neurological outcomes in patients with myelopathy after ACDA, in contrast to the pre-existing notion that ACDA leads to less favorable outcomes in myelopathy due to micro-trauma caused by preserved mobility [38]. Moreover, additional adjacent segment surgery rates are significantly lower for ACDA, for single- and multi-level surgeries [39, 40]. The difference in additional adjacent segment surgery rates between ACDA and ACDF increases exponentially with longer follow-up time (Table 1). Despite these long-term benefits of ACDA, it is often discouraged since the clinical outcomes are similar to ACDF, but the implant costs are higher. However, preventing new complaints and additional surgeries due to CASP might be a reason for ACDA to be a more cost-effective technique in the long term. A systematic review of economic evaluations in anterior cervical decompression surgery was conducted by our research group [41]. Indeed, the majority of studies reported ACDA to be the most cost-effective technique despite the higher implant costs. However, literature was highly heterogeneous and of low quality. Hence, although there is increasing evidence suggesting that ACDA might be the more long-term cost-effective technique because of the reduced risk on CASP and associated additional surgery rates compared to ACD(F), the quality of this evidence is lacking, especially in Europe. Therefore, the need for a solid clinical cost-effectiveness trial addressing this question is high. Currently, ACDA cannot be offered as a standard treatment in the Netherlands because it is not reimbursed as the costs for ACDA are higher and short-term symptom relief appears equal between the techniques.

**Table 1 Tab1:** Incidence rates of additional surgery for CASP

	FU time (years)	ACDA (%)	ACDF (%)	Annual rate ACDA (%)	Annual rate ACDF (%)
**Trial registration NCT00389597**					
Radcliff [42]	7	3.7 4.4	13.6 11.3	0.5	1.9
Radcliff [39]	5	3.1	11.4	0.6	2.3
Jackson [43]	5	4.5 7.3	17.3 21	0.9 1.5	3.5 4.2
Radcliff [44]	3	5.7	10.5	1.9	3.5
Davis [45]	2	0.9	0	0.4	0
**Trial registration NCT0029108**					
Loumeau [46]	7	0	18.2	0	2.6
Janssen [47]	7	7	18	1	2.6
Zigler [48] and Delamarter [49]	5	2.9	11.3	0.6	2.3
Murrey [50]	2	1.8	8.5	0.9	4.2
**Trial registration NCT00637156**					
Gornet [51]	10	9	17.9	0.9	1.8
Gornet [52]	7	11.6 6.5	10.9 12.5	0.9	1.8
Lanman [53]	7	6.5	12.5	0.9	1.8
Gornet [54]	2	2.4	3.2	1.2	1.6
**Trial registration NCT642876**					
Burkus [55]	7	4.6	11.9	0.7	1.7
Mummameni [56]	2	1.1	3.4	0.5	1.7
**Trial registration NCT00437190**					
Loidolt [57]	10	9.7	15.8	1.0	1.6
Lavelle [58]	10	9.7	15.8	1.0	1.6
Sasso [59]	4	4.1	4.1	2.8	1.7
Heller [60]	2	2.5	3.6	1.2	1.8
**Average [range]**				**1.0 [0; 2.8]**	**2.2 [0; 4.2]**

Equipoise remains concerning the cost-effectiveness of these techniques; the main aim of CACES is to determine the long-term cost-effectiveness of ACDA in comparison to ACDF. As the difference in re-operation rates for CASP is expected to be lower after ACDA, we hypothesize that the initial higher costs of a disc prosthesis might reimburse itself on the long term. The study aims to investigate a population that reflects daily practice; therefore, both radiculopathy and myelopathy and single- and multi-level patients will be included.

## Methods

### Objectives

The primary objective of the proposed study is to examine whether ACDA is preferred over ACDF in terms of cost-effectiveness from a healthcare and societal perspective, in patients with single- or multi-level symptomatic CDDD. Secondary objectives include differences in clinical and radiological outcomes between the two techniques, as well as the qualitative process surrounding anterior decompression surgery.

### Study design

This is a prospective, single-blinded, randomized controlled trial. One study arm receives ACDA (intervention group), and the other receives ACDF (control group). Patients will be randomized in a computer-generated 1:1 ratio to ensure equal division among both groups. No block randomization or stratification will be used. Only the coordinating investigator will be able to perform the computer-generated randomization. Group allocation will be performed per patient, not per level, meaning that no hybrid constructs will be used in this study. CACES investigators and surgeons will not be blinded for treatment allocation. All other involved healthcare professionals are blinded for allocation. All visible documentation will report concerning “ACD,” unspecified whether it concerns fusion or a disc prosthesis. A follow-up period of 4 years was chosen to encompass the expected incidence of 1.6–4.2% of additional CASP-related surgeries of per year, with a peak incidence in the first 2.5 years [16]. It is reasonable to expect that most CASP events will occur within this follow-up period and that we will be able to gather reliable cost data of patients and informal caregivers (ICGs).

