### Outcome measures

All outcomes will be measured at baseline and at 6-month intervals until 4 years post-surgery.

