#### Covariates

Per-operative parameters such as intraoperative complications, operative time, size of the implant, and blood loss will be evaluated. Perioperative complications, re-operations at index- or non-adjacent levels, and their associated costs will be assessed.

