$$d=\frac{average\ NMB\ (ACDF)- average\ NMB\ \left(\mathrm{ACDA}\right)}{Standard\ deviation\ of\ NMB}$$

The standard classification of Cohen’s *d* consists of a small effect (*d* = 0.2), a medium-sized effect (*d* = 0.5), and a large effect (*d* = 0.8) [84].

A two-sided test will be used with a 5% level of significance (*α* = 0.05). A Cohen’s *d* of 0.4 is often referred to as the hinge point, meaning a greater than average effect [84]. We expect a bit less than a medium-sized effect, for which we choose a Cohen’s *d* in between 0.5 and 0.4, resulting in a Cohen’s *d* of 0.45. Inclusion of 79 patients per treatment group will then yield a power of 0.80. Taking into account a 20% loss to follow-up in 4 years, the required sample size is 99 per group, with a total of 198 patients.

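### Simple randomisation cannot guarantee equal arms, and every variable listed under Covariates arises after allocation; the cost is precision, not validity

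*Protocol article*

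**What the plan says.** All references are to the protocol article.

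- **Study design:** "Patients will be randomized in a computer-generated 1:1 ratio to ensure equal division among both groups". The next sentence reads: "No block randomization or stratification will be used".
- **Covariates:** the section consists of two sentences, "Per-operative parameters such as intraoperative complications, operative time, size of the implant, and blood loss will be evaluated" and "Perioperative complications, re-operations at index- or non-adjacent levels, and their associated costs will be assessed". No variable known before randomisation appears under this heading.
- **Outcome measures:** "All outcomes will be measured at baseline and at 6-month intervals until 4 years post-surgery". Under Primary outcome these include the EQ-5D-5L and the productivity questionnaire (iPCQ), so baseline utility and work data are available.
- **Power considerations:** "A two-sided test will be used with a 5% level of significance". The target effect on NMB is set between two conventional values, "resulting in a Cohen’s *d* of 0.45", and then "Inclusion of 79 patients per treatment group will then yield a power of 0.80". Allowing for 20% loss to follow-up, this becomes 99 per group, 198 in all.
- **Statistical analysis:** neither specifies nor excludes adjustment of the primary comparison for baseline values.

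**The concern.** There are two separate faults.

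First, a method is described as securing something it cannot secure. A computer-generated 1:1 list without blocks gives equal numbers only on average, and without strata it gives balance of prognosis only on average.

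Second, the one section that names covariates names the wrong kind. Operative time, implant size, blood loss, complications and re-operations all follow allocation and can be affected by the technique. The costs of complications and re-operations are also part of the societal cost in the primary outcome. A model for NMB that included them would remove part of the effect being estimated. The article does not announce such a model, but the heading invites it.

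The choice matters because the population is mixed on purpose: radiculopathy and/or myelopathy, up to four levels, any age from 18. Power considerations expects most of the cost difference to come from episodes of secondary symptoms and lists absence from work among their consequences. Whether a patient is in paid work is therefore likely to be strongly prognostic for costs, and baseline utility for QALYs. If the primary comparison uses neither, that variation stays in the error term.

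**Working it through.** **1. The plan's own sample size.** Inputs from Power considerations: d = 0.45, two-sided α = 0.05, power 0.80, 20% loss.

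- Normal approximation: n = 2(1.96 + 0.842)²/0.45² = 77.5, rounded up to 78.
- Two-sample t-test: 78.49, rounded up to 79, with power 0.803.
- Allowing for loss: 79/0.8 = 98.75, rounded up to 99 per group, 198 in total.

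The stated figures are reproduced.

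**2. Does the allocation method ensure equal division?** Under simple randomisation the size of one arm is Binomial(198, 0.5).

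- P(exactly 99:99) = 0.057.
- 95% range for one arm: 85 to 113.
- P(arms differ by 10 or more) = 0.52; by 20 or more, 0.18.
- Power at 85:113 after 20% loss: 0.796, against 0.803 for equal arms.

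The claim is wrong, but unequal numbers cost almost nothing.

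**3. Balance of prognosis.** For a standardised baseline covariate at 79 per group, the SE of the difference between arms is √(2/79) = 0.159 SD, with a 95% limit of ±0.31 SD.

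- P(one given covariate differs by 0.2 SD or more) = 0.21; P(at least one of three independent covariates does) = 0.50.
- A binary factor with 50% prevalence (assumed): 95% limit ±15.6 percentage points; P(difference of 10 points or more) = 0.21.
- The shift carried into NMB is correlation × imbalance. At an assumed correlation of 0.5 its 95% limit is 0.5 × 0.31 = 0.16 SD, about 35% of the target d = 0.45. At 0.7 it is 0.22 SD, about 49%.

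This variation is already part of the standard error of an unadjusted comparison. It does not raise the type I error rate.

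**4. What baseline adjustment would gain.** Adjusting for covariates with correlation r with NMB multiplies the residual SD by √(1 − r²). The n needed is 79(1 − r²). Power is by the normal approximation, whose unadjusted value at 79 per group is 0.81. The article gives no value of r, so a range is shown.

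| r (assumed) | Power at 79 per group | n per group needed |
|---|---|---|
| 0 | 0.81 | 79 |
| 0.3 | 0.84 | 72 |
| 0.5 | 0.90 | 60 |
| 0.7 | 0.98 | 41 |

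**5. Timing of the listed covariates.** The first sentence of the Covariates section is confined to the operation. The second covers the perioperative period and later re-operations, with their costs. Every item comes after allocation. Against this, baseline utility, baseline work data, number of levels and presence of myelopathy are all collected or known before surgery.

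**The case against.** Four points can fairly be made in the plan's defence.

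- **Scope.** The choice of model covariates is commonly left to the SAP, which is not shown, and the article collects the baseline data that adjustment would need. This stands: silence on baseline adjustment would not by itself be a finding. What remains is what the article does state, namely an equal-division claim that its method cannot deliver and a Covariates section made up wholly of post-allocation variables.
- **No biased analysis is announced.** The listed items are to be evaluated and assessed, not adjusted for. This also stands. The fault lies in the label and in what it may lead to.
- **Validity is intact.** Chance imbalance under simple randomisation is covered by the standard error. This stands.
- **Simple randomisation has a merit here.** In a single centre, with unblinded surgeons and investigators and one coordinating investigator performing the randomisation, it is the least predictable method. Stratified blocks would trade some of that away, so they cannot be called a required correction.

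A reader might go further and infer that chance imbalance could exceed the effect the trial seeks. The document does not support this. The effect sought is d = 0.45. A single covariate imbalance larger than 0.45 SD has probability about 0.005 at 79 per group, and at correlation 0.5 a shift in NMB of that size has probability about 1.5 × 10⁻⁸.

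The inference looks better only against a net saving derived from the article's cost inputs: 4 × (2.2% − 1.0%) = 0.048 fewer operations per patient; 0.048 × (€11,000 + 242 × €250) − 1.2 × €1,500 = €1,632. One SE of imbalance in paid work, if 60% work (assumed), is √(2 × 0.6 × 0.4/99) = 0.070, worth about €4,200 at €60,500 per episode. But the article does not state €1,632 as its target, and both figures count every day of absence. The article prescribes the friction cost method, which would normally limit the days counted. At an assumed 60 to 115 days, the same formula gives about −€550 to +€110. A gap between that saving and d = 0.45 is a question about the assumed effect size, not about randomisation.

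**Conclusion.** The point holds in a limited form. The equal-division claim is incorrect, with a 5.7% chance of 99:99 and a 95% range of 85 to 113 per arm, but its effect on power is negligible. The Covariates section lists only variables that follow allocation and are unsuitable for adjusting the primary comparison; the article does not say that they will be so used.

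An unadjusted primary test remains valid at 5%. The loss is precision, and its size depends on how strongly baseline values predict NMB, which the document does not give. Over assumed correlations of 0.3 to 0.7, the power forgone at 79 per group runs from about 3 to 17 percentage points (0.84 − 0.81 to 0.98 − 0.81). Number of levels contributes little through implant cost alone: at an assumed SD of 0.4 to 0.5 levels, the 95% limit of imbalance is worth about €190 to €230. The gain would come mainly from utility and paid work. This is a worthwhile improvement and leaves the planned sample size valid; it does not show that the trial would mislead.

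**What to change.** 1. Estimate the primary incremental NMB (or costs and QALYs jointly) with adjustment for values fixed before randomisation: baseline EQ-5D-5L utility, baseline paid work, number of levels and presence of myelopathy. Name these in advance.
2. Retitle the Covariates section, and state that its items are outcomes to be described by arm and will not be used to adjust the primary comparison.
3. Delete the clause in Study design that gives equal division as the purpose of 1:1 allocation.
4. Optional: stratify the remaining allocations, for example by number of levels and paid work, with varying block sizes. Weigh this against the added predictability in a single centre with unblinded investigators. Keeping simple randomisation is acceptable.

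Items 1 to 3 need only wording in the protocol and the SAP, with no new data and no change to the 198 patients. Item 4 would need a change to the randomisation tool.

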### Interventions

One of two surgical procedures will be performed on patients participating in this study: ACDA (intervention group) and ACDF (control group). In both techniques, the disc space is approached through a right- or left-sided anterior surgical approach. The disc content will be removed, after which the endplates are prepared with curettes. The posterior longitudinal ligament is opened, and the dura is visualized to ensure adequate decompression. In the ACDF group, a cage (CeSPACE® XP) is implanted; in the ACDA group, a disc prosthesis (ActivC®) is implanted after the discectomy. No bone substitutes will be used.

Implantation of the devices is done in accordance with the manufacturer’s protocol for implantation and endplate preparation. In both groups, the wound is closed in layers, after a prevertebral wound drain is placed. Potential surgical risks are similar between the cage (ACDF) and the arthroplasty group (ACDA) [38, 61].

Post-surgical care is the same for both groups. Patients receive 24 h of antibiotic prophylaxis, and after 24 h, the prevertebral wound drain is removed. Patients can use analgesics post-operatively, and they are allowed to mobilize immediately. The day after surgery, a physical therapist provides patients with standardized exercises. Patients are not routinely referred to a physical therapist, and no neck collar is used.

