### Implementation plan

Figure 1 depicts the flowchart of the study process. Patients will be selected by screening the appointments in the neurosurgical outpatient clinic the waiting lists for surgery. When a patient is indicated to undergo anterior cervical decompression surgery, the treating neurosurgeon will inform the patient about the CACES trial. The patient is contacted by the investigator to provide extensive information. Additionally, written information is sent to them by (e)mail. A week after the information is sent, the investigator contacts the patient again to answer remaining questions. Patients are included in the study when informed consent is signed. Data is collected in the research manager tool, which is a database with a built-in auditing system. Questionnaires, including reminders, are sent automatically once the patient is registered in Research Manager. If patients or informal caregivers prefer to fill out questionnaires on paper, the answers will be registered in Research Manager by the investigator and the paper version will be stored. Data will be collected at baseline and at 6-month intervals until 4 years post-surgery. The patients will be blinded to their received treatment for the first year after surgery to obtain more reliable patient-reported outcome measures (PROMs). After 1 year, patients will have an outpatient appointment with the coordinating investigator for unblinding (if wanted) and additional imaging.

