#### Secondary outcomes

Secondary outcomes will consist of both clinical and radiological outcome measurements.

Clinical outcomes will be assessed according to the rate of CASP and associated additional surgeries, combined with patient-reported outcome measures (PROMs). The included PROMs are the Neck Disability Index (NDI) [69], Visual Analogue Scale (VAS) [70] for neck and arm pain, Hospital Anxiety Depression Scale (HADS) [71], and the modified Japanese Orthopedic Association score (mJOA) [72] for myelopathy or myeloradiculopathy patients. CASP is defined as the presence of newly developed symptomatic cervical radiculopathy and/or myelopathy on a level adjacent to the initial surgery, confirmed by corresponding findings upon magnetic resonance imaging (MRI). It should be noted that *RASP* is differentiated from *CASP* by the presence of clinical symptoms that are attributed to the degenerative changes for the latter. Patients were only considered as having CASP when new clinical symptoms developed. Additional adjacent segment surgery for CASP was defined as surgery for radiculopathy and/or myelopathy at a segment adjacent to the level of initial surgery. Notably, neck pain itself is not considered as a surgical indication in our national guidelines [73]. Re-operations at the index level and at levels not adjacent to the initially operated level were not considered as additional surgery for CASP.

Radiological outcomes will be assessed at three time points: pre-operative, directly post-operative, and 1 year post-operative. Pre-operative imaging will assess baseline degeneration according to the Kellgren-Lawrence Score (KS) [74], cervical sagittal alignment, and baseline disc height. Moreover, a full sagittal spine X-ray will be taken to assess pre-operative global balance according to the odontoid-hip axis (OD-HA) [75]. A standard cervical spine X-ray will be taken at the immediate post-operative period (before discharge) to assess the position of the implant, subsidence, and cervical sagittal alignment. Cervical spine X-rays will be taken again 1 year post-operative to assess fusion, cage subsidence, adjacent segment degeneration (KS), adjacent segment disc height, and alignment. A flexion and extension X-ray will be taken to assess movement. Radiological cage subsidence will be defined as > 3-mm decrease of interbody height compared to the direct post-operative X-ray [76, 77].

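### The blinding claim for all other professionals is too broad: the planned post-operative X-rays show the implant, and the adjacent-level readings come from the same 1-year films

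*Protocol article*

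**What the plan says.** Under Study design, the Protocol article gives the trial's label: "This is a prospective, single-blinded, randomized controlled trial". It names who knows the arm: "CACES investigators and surgeons will not be blinded for treatment allocation". It then makes a statement about everyone else: "All other involved healthcare professionals are blinded for allocation". The only means it gives is a rule about documents: "All visible documentation will report concerning “ACD,” unspecified whether it concerns fusion or a disc prosthesis".

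Under Interventions, the arms differ in the implanted device: "In the ACDF group, a cage (CeSPACE® XP) is implanted; in the ACDA group, a disc prosthesis (ActivC®) is implanted after the discectomy".

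Under Secondary outcomes, the first post-operative X-ray is described with the words "before discharge) to assess the position of the implant, subsidence, and cervical sagittal alignment". The 1-year X-rays are taken "to assess fusion, cage subsidence, adjacent segment degeneration (KS), adjacent segment disc height, and alignment", together with a flexion-extension film for movement.

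On patients, the Implementation plan says: "The patients will be blinded to their received treatment for the first year after surgery".

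**The concern.** The blinding statement covers every professional except two named groups. A single group that has to look at the implant is enough to make it untrue as written. Neutral wording on a form or letter does nothing to hide an image.

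What is at stake is the adjacent-level radiological reading. The Introduction says that arthroplasty was developed to spare adjacent segments by preserving motion, and the Discussion says the trial will evaluate the factors proposed to accelerate adjacent segment pathology. A grade of degeneration involves judgement. If it is made with the implant in the same picture, the reader's expectation about the two techniques can enter it. A lesser matter is the pre-discharge film: it is taken inside the year in which patients are blinded, and the safeguard described covers documents only.

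**Working it through.** No figure in the plan is at issue, so the check sets the sections side by side.

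1. **Who is said to be blinded.** Study design names investigators and surgeons as unblinded and everyone else involved as blinded, with no exception for staff who handle images.

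2. **How.** The only measure described is that visible documents use a term common to both procedures. Images are not mentioned.

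3. **What the films show.** The pre-discharge film is taken to judge implant position and subsidence. The 1-year films are taken to judge fusion, cage subsidence and movement. Each of these requires looking at the operated level, so whoever takes or reads the film sees the device.

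4. **Can the arm be inferred from the film?** The article does not describe how either device looks on X-ray, so this step is an inference. It is a strong one. The devices are of different kinds. The Introduction reports fusion in 95–100% of cases after ACDF and describes ACDA as preserving motion in the operated segment. Flexion-extension films, which are taken to assess movement, would therefore tend to separate the arms even if static films did not.

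5. **Where the adjacent level is read.** The Kellgren-Lawrence grade (KS) and adjacent disc height appear in the same list of 1-year readings as fusion and cage subsidence. Two cases cover the possible readers:
   - An investigator or surgeon reads the films. This person is openly unblinded under Study design.
   - Someone else reads them. This person is blinded according to the statement, but the implant is in the film being read.

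   In both cases the adjacent level can, as written, be scored with the arm in view.

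6. **Which film falls in the blinded year.** The pre-discharge film does. The 1-year imaging is tied to the visit at which patients may learn their arm, so it coincides with the planned end of patient blinding.

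7. **Workload of the remedy.** The planned total is 198 patients. One pre-operative and one 1-year set each gives 198 × 2 = 396, about 400 sets, and fewer if patients drop out before 1 year.

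**The case against.** The other side has several good arguments.

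- **The trial is labelled single-blinded, and the article never says that the film reader is blinded or who reads.** This is correct. If investigators or surgeons read the films, the reading contradicts nothing in Study design. A reader might infer that the trial report will describe its radiological reader as blinded; the document does not support that.
- **Reader identity, reading order and masking are details that an article usually leaves to the full protocol.** This is also fair, and their absence is not the point raised here. A masked reader named in the full protocol would settle the grading question. It would not rescue the universal sentence, because staff who take the films or read them for care would still see the device.
- **Cage subsidence need not reveal the arm.** One might infer that it can be scored only by someone who knows a cage is present. The article defines it as a loss of more than 3 mm in interbody height against the first post-operative film, which is a height measurement, so that argument is not used.
- **Patient blinding.** One might infer that staff will tell patients their implant. No section describes such access or disclosure. All that can be said is that the written safeguard does not extend to images.
- **Importance.** One might infer that the trial's main result is exposed. The primary outcome rests on costs and on QALYs from EQ-5D-5L at 4 years. Clinical adjacent segment pathology is defined separately and needs new symptoms confirmed on MRI. The KS grade and disc height at 1 year feed neither the primary analysis nor the sample size.
- **Feasibility.** Up to 4 consecutive levels may be operated on, and an adjacent disc shares a vertebra with the operated level. Masking may not work in every film.

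What stands against all of this is the over-broad sentence, and adjacent-level readings that come from films showing the implant, whoever reads them.

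**Conclusion.** The point holds in a limited form. The statement that all other professionals are blinded cannot be relied on for staff who take or read the post-operative X-rays. Professionals who never see the films can remain blinded. The secondary readings of KS grade and adjacent disc height can, as written, be made with the arm in view.

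This rests on one assumption outside the text: that a cage and a disc prosthesis can be told apart on X-ray.

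No size can be put on the bias. One might be tempted to calculate an inflated false-positive rate, but the article gives no rate of adjacent-level worsening, no measure of reader bias and no binary worsening endpoint, so any such number would only reflect what was assumed. The effect is confined to secondary radiological outcomes, with no direct effect on the primary cost-effectiveness result. The change is still worth making, because the statement is inaccurate and the remedy is cheap.

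**What to change.** 1. **Narrow the statement in Study design.** Limit it to patients during the first year and to professionals without access to post-operative images.
2. **Set a reading order.** Whoever already reads the films scores KS grade and adjacent disc height first, on de-identified pre-operative and 1-year images in random order, with the operated level or levels masked where feasible. Only then is the full film opened for fusion, subsidence, alignment and movement. Where masking is not feasible, report the reading as unblinded.
3. **Extend the existing documentation safeguard to images.** Post-operative images should not be shown or described to patients before the 1-year visit.

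The cost is one corrected sentence, a short reading instruction, a staff instruction, and the time to crop about 400 film sets. No additional reader, visit or film is required. Stored films can be read this way even though recruitment has begun. The drawback is a less favourable blinding statement.
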